## Abstract

**Background:**

Reduced sleep quality is a common complaint among patients with chronic pain, with 50-80% of patients reporting sleep disturbance. Improvements in pain and quality of life measures have been achieved using a multidisciplinary cognitive behavioural therapy pain management programme (CBT-PMP) that aims to recondition attitudes to pain, and improve patients' self-management of their condition. Despite its high prevalence in patients with chronic pain, there is very limited objective evidence for the effect of this intervention on sleep quality. The primary research objective is to investigate the short-term effect of a multidisciplinary CBT-PMP on subjective (measured by Pittsburg Sleep Quality Index) and objective sleep quality (measured by Actigraphy) in patients with chronic pain by comparison with a control group. The secondary objectives will investigate changes in function and mood, and then explore the relationship between objective and subjective sleep quality and physical and psychological outcome measures.

**Methods/Design:**

Patients who fulfil the inclusion criteria for attendance on the multidisciplinary CBT-PMP in the Adelaide and Meath Hospital, Tallaght, Dublin and are currently listed on the PMP waiting list will be invited to participate in this pilot study. Potential patients will be screened for sleep disturbance [determined by the Pittsburgh Sleep Quality Index (PSQI)]. Those patients with a sleep disturbance (PSQI >5) will be assigned to either the intervention group (immediate treatment), or control group (deferred treatment, i.e. the PMP they are listed for is more than six months away) based on where they appear on the waiting list. Baseline measures of sleep, function, and mood will be obtained using a combination of self-report questionnaires (the Hospital Anxiety and Depression Scale, the Short Form 36 health survey, the Pittsburgh Sleep Quality Index, the Tampa Scale for Kinesiophobia), and functional outcome measures. Sleep will be measured for seven days using actigraphy (Actiwatch 7). These measures will be repeated after the four week multidisciplinary cognitive behavioural therapy pain management programme, and at a two month follow-up. The waiting list control group will be assessed at baseline, and two months later. Analysis for the primary outcome will include between group differences of subjective and objective sleep parameters from baseline to follow-up using Independent T-tests or Mann-Whitney U tests. The secondary outcomes establishing relationships between the sleep variables and physical and psychological outcome measures will be established using multiple linear regression models.

**Discussion:**

This pilot study will evaluate the impact of a multidisciplinary CBT-PMP on both subjective and objective measures of sleep in patients with chronic pain and provide guidance for a larger clinical trial.

**Trial Registration:**

Current controlled trial ISRCTN: ISRCTN74913595

## Background

Chronic pain is a common disorder affecting 19% of the European population. It has a detrimental effect on all aspects of patient's quality of life: physically, psychologically, and socially [1]. Reduced sleep quality is a common complaint in this patient cohort with 50-80% reporting sleep disturbance [1,2]. Increasing evidence suggests a deteriorating cycle of pain and sleep. Pain can lead to poor sleep which in turn may result in increased next day pain, leading to further problems with next night sleep, as seen in other chronic pain conditions such as burns and fibromyalgia [3-6]. Whether cause or consequence, sleep disorders must be taken into account in the overall management of the patient in the same way as pain [7], as it has been hypothesized that better daytime pain control may lead to improved sleep quality [8]. Sleep disturbance has been shown to have a number of negative effects on both physical and psychological well-being. Physical effects include a reduction of physical functioning, lowered immune function, lower pain threshold [9], and an increase in the release of pro-inflammatory cytokines [10-13]. Psychologically, patient's mental capacity to manage pain is lowered, with increased risk of anxiety disorders and alcohol abuse [14-16]. Depression is also strongly associated with disturbed sleep patterns in this atient cohort [17-19].

International best practice for the management of chronic pain includes careful pharmacological management, promotion of activity, and the provision of a cognitive behavioural therapy pain management programme (CBT PMP) [20]. This multi-disciplinary intervention based on cognitive behavioural principles aimed at educating chronic pain patients on the physiology and psychology of chronic pain, healthy functioning, and the self-management of their pain problem. [21]. The programme includes daily clinical psychology (cognitive behavioural therapy, relaxation techniques), physiotherapy (progressive gym exercise programme), and occupational therapy (improving occupational function and environmental adaption).

The positive effect of this intervention on pain, disability, and mood has been established in two recent systematic reviews [22,23]. However, despite the known relationship between pain and sleep quality in this patient cohort, the impact of CBT-PMPs on sleep is limited. Significant positive changes in subjective sleep disturbances have been reported, however sleep was not the primary outcome measure, and no specific validated subjective or objective sleep quality measures were used [24]. A second study using both objective (actigraphy) and subjective outcome measures (PSQI) did report significant differences in sleep quality pre and post CBT PMP and at a three-month follow-up (P < 0.05) [25]. However, the main conclusions were drawn from the subjective data only. More recently a randomised controlled trial of individual cognitive behavioural therapy intervention for insomnia, delivered by a psychologist, demonstrated significant improvement in subjective and objective sleep indices for patients with chronic neck and back pain [26]. Drawing conclusions from subjective sleep quality outcome measures is limiting; objective and subjective sleep measures only correlate modestly with each other, therefore both should be included [27-30].

Due to the limited objective evidence to date, this pilot study will determine the short-term impact of a CBT-PMP on changes in objective and subjective sleep quality measures, as well as the impact of these changes on patient's psychological and physical measures.

## Method/Design

### Research Objectives

The primary research objective is to investigate the short-term multidisciplinary CBT-PMP on subjective (measured by PSQI) and objective sleep quality (measured by Actigraphy) in patients with chronic pain by comparison with a control group. The secondary objective will investigate changes in function and mood, and then explore the relationship between objective and subjective sleep quality, and physical and psychological outcome measures.

### Ethical Approval

This study was granted ethical approval from the Adelaide and Meath Hospital, Incorporating the National Children's Hospital Healthcare Group, Ethics and Medical Research Committee in October 2007.

### Study Design

This study is a longitudinal pilot study, with patients recruited from the adult Pain service in the Adelaide and Meath Hospital, Dublin (Figure 1). Potential patients who fulfil the inclusion criteria for participation on the multidisciplinary CBT-PMP will be invited to participate in the study by the principle investigator (PI). The study protocol will be reviewed with potential participants, and all questions answered regarding the study. One week later, following a cooling off period, written consent will be obtained, and participants will complete the Pittsburgh Sleep Quality Index (PSQI). Those patients with a sleep disturbance (PSQI >5) will be assigned to either the intervention group (immediate treatment), or control group (deferred treatment, i.e. the PMP they are listed for is more than six months away) based on where they appear on the waiting list. Group membership will be concealed from the PI. To be eligible to take part in the study, participants must fulfil the following criteria:

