#### Study Patients

One week prior to the commencement of the multidisciplinary CBT-PMP patients will be given an appointment with the PI to obtain baseline measures. This will involve completing the self-report questionnaires and undergoing the physical tests. Patients will be instructed to wear the Actiwatch for seven days (24 hours a day), and to complete the Pittsburgh Sleep diary (PghSD) during this time. Following the four week CBT-PMP the patients will be reassessed, given the Actiwatch to wear for seven days, and complete the sleep diary. Two months later, one week prior to the appointment date patients will be sent (by registered post) the Actiwatch to wear for seven days, and the PghSD to complete. During the appointment patients will repeat the battery of self-report and functional tests.

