#### Control Group

Patients will undergo the same assessment procedures at baseline and three months later.

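### The unqualified statement that group membership is concealed from the PI is not secured by the assessment schedule the article describes

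*Protocol article*

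**What the plan says.** Study Design states "Group membership will be concealed from the PI". The sentence directly follows the assignment rule and carries no qualification.

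The same section has the PI invite the patients. It assigns them without randomisation, by waiting-list order; the deferred arm consists of patients whose programme is over six months off.

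For the intervention group, the Study Patients section sets three assessments:
- Baseline: "One week prior to the commencement of the multidisciplinary CBT-PMP patients will be given an appointment with the PI to obtain baseline measures".
- End of programme: "Following the four week CBT-PMP the patients will be reassessed, given the Actiwatch to wear for seven days, and complete the sleep diary".
- Follow-up: "Two months later, one week prior to the appointment date patients will be sent (by registered post) the Actiwatch", with the questionnaires and function tests repeated at the appointment.

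For controls, the Control Group section says "Patients will undergo the same assessment procedures at baseline and three months later". The abstract differs on the interval: "The waiting list control group will be assessed at baseline, and two months later". Both give controls two assessments.

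**The concern.** Placed straight after the assignment rule, the sentence most naturally means that from assignment onwards the PI does not know who is in which group. A reader would take that as protection against assessor bias. It would matter here, because assignment follows waiting-list order and there is no randomisation to rely on.

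Three parts of the data could be affected by an assessor who knows the group:
- **Timed function tests** (Function section). Sit-to-stand and rollover are timed performances, open to differences in encouragement and timing.
- **The actigraphy sleep window** (Sleep section). Where a button press is missed, sleep start or finish is taken from the diary. That window feeds every actigraphy parameter, and objective sleep is part of the primary outcome.
- **Administration of the self-report measures**, to a lesser degree.

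The pilot is also meant to guide a larger trial, so a description of masking that the design does not support could be carried forward.

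**Working it through.** The plan gives no figure on this point, so the check sets the two schedules side by side. Months are converted at 52.18 / 12 = 4.35 weeks, and time is counted from each patient's own baseline.

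| | Intervention | Control |
|---|---|---|
| Programme start | week 1 | more than 6 × 4.35 = 26.1 weeks after assignment |
| Baseline assessment | week 0, with the PI | week 0, assessor and calendar timing not stated |
| End-of-programme assessment | 1 + 4 = week 5, assessor not named | none |
| Follow-up | 5 + 2 × 4.35 = week 13.7, assessor not named | 3 × 4.35 = week 13.0 (Control Group section) or 2 × 4.35 = week 8.7 (abstract) |
| Number of assessments | 3 | 2 |

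**Baseline.** The intervention visit is tied to a programme one week off. A control's visit cannot be, because that patient's programme is over six months away. The appointment date is therefore a cue to group for anyone who knows why it was chosen. It is not proof: the calendar timing of control baselines is not given, and if controls are seen in the same weeks the date alone says little.

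**End of programme.** Only intervention patients can have this visit. At either stated control follow-up (week 8.7 or 13.0) a control has not yet started the programme. Whoever conducts or sees the visit knows the group with certainty. At the planned 24 per arm, the study has 24 × 3 + 24 × 2 = 120 assessments, of which 24 (20%) are of this kind. They cover every intervention patient who attends.

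**Invitation and screening.** Waiting-list position decides the group. The article does not say that the PI sees list positions or programme dates, so concealment could hold at this step.

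**Safeguards described.** None of the sections shown describes a second assessor, an independent scheduler or a masking procedure. The Data management section codes participant data, but for anonymity; it does not say that the code hides group or visit.

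The disagreement between two and three months for control follow-up is a separate matter that needs reconciling. It does not change the visit count.

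**The case against.** The strongest reply is that the text never puts the PI at the visits that reveal the group. The PI is named for two acts only, inviting patients and the baseline appointment. The later visits are written in the passive, so another assessor is possible. The sentence stands in Study Design, not under Assessment or Data Analysis, and may be meant only for invitation and screening, where it could be true. The article does not call any assessor blinded. It is a condensed account, and its study flow figure is not available here.

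The harm is also limited for the primary outcome. The PSQI is self-completed and the Actiwatch scores automatically. The patient's button presses define the sleep period, and the fallback is the patient's own diary. The article does not say that the PI sets those windows. The function tests are secondary.

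Much of this stands. It rules out a stronger reading that a reader might infer: that the PI is certainly unmasked for every intervention patient, or that the trial claims assessor blinding and lacks it. It does not rescue the sentence as written. The sentence is unlimited, and the baseline visit, where the PI is named, already ties intervention patients to an imminent programme. Nor is this simply detail left to a fuller document, because the article makes a positive statement that its own schedule does not support.

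**Conclusion.** The concern holds in limited form: the article asserts a property that the schedule it describes does not secure. Concealment may hold at invitation and PSQI screening. It is weakened at baseline if the PI knows why the appointment date was chosen. It is lost at the end-of-programme assessment at the latest, for up to 24 planned intervention patients, if the PI conducts or sees that visit.

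The conclusion rests on the visit counts of three against two, which the text gives plainly, and on the absence of any named assessor other than the PI. That the PI performs all assessments is an assumption, not a stated fact. No size of bias can be derived. Any effect would fall mainly on the timed function tests, and for actigraphy mainly on nights where the diary sets the window. This should be corrected, but it does not invalidate the pilot.

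**What to change.** 1. Limit the concealment sentence to the stage at which it can hold, for example invitation and PSQI screening, or remove it. State who performs each assessment, and do not present later assessments by the PI as blinded.
2. Give each Actiwatch file and its diary a code that hides both group and visit. Set all sleep start and finish times on the coded files, including those taken from the diary, and run the software before the code is broken. The person setting the windows should not hold the key.
3. If the PI performs the sit-to-stand and rollover tests, report them as unblinded secondary outcomes.

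The cost is a change of wording, a small amount of file-coding work, and a less favourable description of blinding. No visit or patient is added, and the assessment schedule stays as it is.

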**Figure 1 F1:**
[figure not shown]
**Study Protocol**.

#### Inclusion Criteria

• Deemed suitable for the AMNCH multidisciplinary CBT-PMP as per the multidisciplinary pain team

• Willing to participate in the study

• > 18 years old

• Suffering from sleep disturbance due to pain as determined by the PSQI questionnaire

• (a score >5 indicating sleep disturbance)

#### Exclusion Criteria

• Deemed unsuitable for the AMNCH multidisciplinary CBT-PMP as per the multidisciplinary pain team

• Unwilling to take part in the study

• <18 years old

• Do not suffer from sleep disturbance due to pain as determined by the PSQI questionnaire (a score >5 indicating sleep disturbance)

### Intervention

A multi-disciplinary CBT-PMP provides the patient with multiple therapies involving comprehensive rehabilitation in each of the specialized areas [31]. The core multi-disciplinary team includes a pain management physician, an occupational therapist, a physiotherapist and a clinical psychologist. They identify and change unhelpful thoughts and beliefs; promote relaxation, and help to change habits that contribute to disability [21,22].The multi-disciplinary team focuses on specific achievable goals established between the individual therapist and the patient [32]. Participants are advised to practice the skills they have learned both at home, and in other environments, integrating them into their everyday lives in order to help them to manage their pain more effectively [21].

Participants will attend three days a week for four consecutive weeks. The multidisciplinary programme includes daily two-hour group sessions with physiotherapy (stretching programme, core stability strengthening programme, paced individual exercise on a range of gym equipment, and functional restoration), occupational therapy (improving occupational function and environmental adaption), and clinical psychology (cognitive behavioural therapy, relaxation techniques). Weekly education sessions with the Pain consultant are also held.

### Assessment

A combination of valid and reliable self-report measures of pain, sleep quality, quality of life, nd mood, as well as objective measures of function and sleep will be used.

#### Study Patients

One week prior to the commencement of the multidisciplinary CBT-PMP patients will be given an appointment with the PI to obtain baseline measures. This will involve completing the self-report questionnaires and undergoing the physical tests. Patients will be instructed to wear the Actiwatch for seven days (24 hours a day), and to complete the Pittsburgh Sleep diary (PghSD) during this time. Following the four week CBT-PMP the patients will be reassessed, given the Actiwatch to wear for seven days, and complete the sleep diary. Two months later, one week prior to the appointment date patients will be sent (by registered post) the Actiwatch to wear for seven days, and the PghSD to complete. During the appointment patients will repeat the battery of self-report and functional tests.

#### Control Group

Patients will undergo the same assessment procedures at baseline and three months later.

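### The control group's only follow-up is dated two months after baseline in the Abstract and three months in the Assessment section; at two months it falls five weeks short of the intervention group's interval

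*Protocol article*

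**What the plan says.** The control group's follow-up is dated in two places:

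- Abstract, Methods/Design: "The waiting list control group will be assessed at baseline, and two months later".
- Assessment, Control Group: "Patients will undergo the same assessment procedures at baseline and three months later".

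The intervention group's schedule is in Assessment, Study Patients, with the programme length in Intervention:

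- Baseline: "One week prior to the commencement of the multidisciplinary CBT-PMP patients will be given an appointment with the PI to obtain baseline measures".
- Programme: "Participants will attend three days a week for four consecutive weeks".
- End of programme: "Following the four week CBT-PMP the patients will be reassessed, given the Actiwatch to wear for seven days, and complete the sleep diary".
- Last visit: "Two months later, one week prior to the appointment date patients will be sent (by registered post) the Actiwatch to wear for seven days".

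The Abstract condenses this schedule: "These measures will be repeated after the four week multidisciplinary cognitive behavioural therapy pain management programme, and at a two month follow-up".

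Data Analysis compares the groups on change in the objective and self-reported sleep measures between baseline and follow-up, by independent t test or Mann-Whitney U test. It does not say which of the intervention group's two later visits counts as follow-up.

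**The concern.** The two control dates cannot both be right. They describe the same group and the same single visit after baseline. Since controls are not due to start the programme for more than six months, either date is practicable, so feasibility does not show which one is meant.

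The date matters because the primary analysis is a plain comparison of change scores. That comparison isolates treatment only if both groups are observed over the same length of time. Neither planned test adjusts for elapsed time, and with one control visit after baseline there is no other between-group contrast to fall back on.

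Patients enter with a PSQI above 5, and groups are formed by waiting-list position. Regression to the mean, the natural course of the condition and season can all move sleep scores without treatment. Where the intervals differ, whatever such change accrues in the extra weeks is attributed to the programme.

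**Working it through.** The check is timeline arithmetic. The one assumption is the length of a month, taken as 4.0 weeks or as 365.25 / 12 / 7 = 4.35 weeks.

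**Inputs**
- Baseline to programme start: 1 week (Study Patients)
- Programme: 4 weeks (Intervention)
- End-of-programme reassessment to last visit: 2 months (Study Patients)
- Control visit: 2 months (Abstract) or 3 months (Control Group)

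**Intervention interval** = 1 + 4 + 2 × month
- Month of 4.0 weeks: 1 + 4 + 8.0 = 13.0 weeks
- Month of 4.35 weeks: 1 + 4 + 8.7 = 13.7 weeks

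**Gap between the groups**

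| Control visit | Weeks from baseline (4.0 / 4.35) | Intervention minus control |
|---|---|---|
| 2 months | 8.0 / 8.7 | 5.0 / 5.0 weeks |
| 3 months | 12.0 / 13.0 | 1.0 / 0.7 weeks |

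In the two-month version the month length cancels: (1 + 4 + 2 months) − 2 months = 5 weeks. As a share of the intervention interval this is 5 / 13.7 = 36% to 5 / 13.0 = 38%.

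**Sensitivity to the reassessment date.** The article says only that reassessment follows the programme. If it falls a week after the programme ends and the two months run from there, each gap grows by one week: to 6.0 weeks in the two-month version, and to 1.7 to 2.0 weeks in the three-month version.

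**Which intervention visit is follow-up.** If the end-of-programme visit (1 + 4 = week 5) were used instead, it would match neither control date:
- Two-month control visit: 8.0 − 5 = 3.0 to 8.7 − 5 = 3.7 weeks later
- Three-month control visit: 12.0 − 5 = 7.0 to 13.0 − 5 = 8.0 weeks later

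Only the pairing of the last intervention visit with the three-month control visit comes close to equal intervals.

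**The case against.** The best defence is that the working schedule is nearly sound. The three-month date stands in the Assessment section, directly after the detailed intervention schedule, and falls within about a week of the intervention group's last visit. The two-month date appears only in the Abstract, just after a mention of a two-month follow-up, and may be no more than loose condensation. This stands: the three-month version is the more likely intention, and if it is followed the remaining misalignment is small. It does not remove the contradiction, because the document still gives two dates for one visit.

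One might also read the Abstract's two-month follow-up as counted from baseline in both groups, which would make them match. The Study Patients text does not support that, since it counts the two months from the end-of-programme reassessment.

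A second defence is that no bias has been demonstrated. Both groups pass the same PSQI threshold, so regression to the mean operates in both, and only what accrues between roughly week 9 and week 14 would distort the contrast. Screening precedes the baseline appointment, so some regression may already have occurred by then. Selection is on PSQI, so the argument is indirect for actigraphy. All of this is fair: the bias is possible, and its size and sign are unknown.

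Finally, this is a pilot of 24 per arm, allocated by waiting-list position, and a common visit window is detail that a journal article may leave to the full protocol. That tempers the weight of the point. But the pilot is meant to inform a larger trial, and a mistimed control change would carry forward into its design.

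**Conclusion.** The concern holds. The article gives two incompatible dates for the only control outcome visit, and that visit determines the primary between-group contrast. The two-month version makes the control interval 5 weeks shorter than the intervention group's 13.0 to 13.7 weeks; the three-month version leaves about 0.7 to 1.0 week.

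This rests on three things: a month of 4.0 to 4.35 weeks, reassessment promptly after the programme, and the intervention group's last visit being the follow-up in the primary analysis. A one-week delay in reassessment adds a week to each gap. Figure 1 is not shown and could not be checked.

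The demonstrated fault is the contradiction and the time gap, not a bias of known size. It should still be corrected before control visits are booked, because measurements taken at the wrong time cannot be recovered.

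**What to change.** Reconcile the Abstract with the Control Group paragraph. State one follow-up interval, in weeks from each patient's own baseline, equal to the intervention group's elapsed time under Study Patients, with the same visit window for both groups.

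In Data Analysis, name this visit as the follow-up for the primary contrast. Add that the intervention group's end-of-programme data are a within-group description only, since the controls have no matching visit.

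The cost is a few sentences and the booking of control appointments. No visits or measurements are added.
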